### Participants

2.2.

For the duration of the study, the Sponsor has taken out insurance covering its own civil liability as well as that of any doctor involved in carrying out the study. He will also ensure full compensation for the harmful consequences of research for the person who lends himself to it and his beneficiaries, unless he can prove that the damage is not attributable to his fault or to that of any intervening party, without that may be opposed the act of a third party or the voluntary withdrawal of the person who had initially consented to participate in the research.

#### Inclusion criteria

2.2.1.

- Patient with suspected chronic osteomyelitis (stage III of the Cierny-Mader classification) of a long bone of the tibia, femur, humerus or forearm, at the diaphysis, metaphysis or epiphysis, defined as follows:o Supposed inoculation >3 months;o At least one of the following clinical signs at the suspected infected site:▪ Spontaneous or bearable pain while walking;▪ Presence of a fistula or history of leakage through a fistula;▪ Presence of serous or purulent flow;▪ Presence of bone exposure;▪ Local inflammation;▪ Fever in the absence of any other explanation.o At least one of the following radiological signs at the suspected infected site:o Bone reshaping with osteolysis or periosteal apposition;o Presence of intramedullary abscess (if Magnetic Resonance Imaging [MRI] performed);o Presence of a fistulous pathway to the intramedullary (if MRI performed);o Presence of bone sequestration visible on CT scan (if CT scan performed).- Patient eligible for conventional surgical treatment of chronic osteomyelitis, with decortication and corticotomy with endomedular debridement (to eradicate bone sequestrums, reduce the inoculum, and identify the bacterium(s) involved) and with secondary intramedullary residual cavity that does not need cementoplasty (osteomyelitis that needs induced membrane technique and cementoplasty are to be considered as stage IV osteomyelitis);- Patient having 3 months of systemic antibiotic therapy post-operatively planned;- If osteosynthetic material is present in the infection site, this material should be considered preoperatively as completely removable during chronic osteomyelitis surgery;- Patient eligible for a direct closure without tension, or eligible for skin and soft-tissue/muscle flap to be performed within 15 days after initial surgery;- Male or female patient between 18 and 80 years of age;- Patient who has given written informed consent to participate in the study;- Geographically stable patient;- Patient able to comply with follow-up visits, protocol schedule and therapeutic treatment, according to investigator’s judgement;- Patient affiliated to or benefiting from a social security system.

#### Exclusion criteria

2.2.2.

- Acute hematogenic osteomyelitis (Cierny-Mader stage I);- Cortical osteitis (Cierny-Mader stage II);- Septic pseudoarthrosis (Cierny-Mader stage IV);- Patient requiring an estimated skin and soft-tissue/muscle flap that cannot be done within 15 days after surgery for the treatment of chronic osteomyelitis;- Female who is pregnant, nursing or who is considering becoming pregnant during the study period;- Patient participating in another interventional study- Patient known to have hypersensitivity to aminoglycosides (especially gentamicin), sulfites (including calcium sulphate) or calcium hydroxyapatite;- Contraindication to the use of Cerament-G: severe myasthenia (class IV or higher according to the MGFA classification), severe renal insufficiency (creatinine clearance <30 ml/min according to the Cockcroft-Gault formula, or GFR < 30 ml/min/1.73m^2^ according to the CKD-EPI or MDRDs equation or, dialysis patient), pre-existing disorders of calcium metabolism (total plasma calcium (or total corrected plasma calcium according to albuminemia) outside normal laboratory values);- Patient with endocrine or metabolic disorders known to affect osteogenesis (e.g., Paget’s disease, renal osteodystrophy, hyperthyroidism, parathyroid disorder, Ehler-Danlos syndrome, osteogenesis imperfecta);- Patient with one or more untreated malignant cancers (including Marjolin’s ulcer), or undergoing radiotherapy or chemotherapy;- Adult patient protected by law, under guardianship or trusteeship.

#### Criteria for early withdrawal from the study

2.2.3.

- Invalidation of the patient’s inclusion by the Patient Eligibility Validation Committee;- Deprogramming and definitive cancelation of surgery for the treatment of chronic osteomyelitis;- Discovery (between the validation of the inclusion and the surgery) of the inability to perform the soft-tissue/muscle flap within 15 days after the initial surgery;- Discovery of hypercalcemia or unknown severe renal failure between the inclusion visit and surgery.

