The pre-surgical visit and the necessary examinations are carried out in accordance with usual practices. Hospitalization for the corticotomy is scheduled in accordance with the usual management no later than 2 months after the inclusion visit in order to limit the risk of canceling the surgery and therefore of the patient leaving the study prematurely.

The eligibility validation committee will meet to validate the patient’s inclusion in the study, based on available clinical data and imaging. If the committee confirms the patient’s eligibility, randomization is carried out and the patient assigned to one of the two study groups: the standard of care (usual medico-surgical management) or the innovative strategy (medico-surgical management with the use of Cerament-G during corticotomy surgery). If the committee invalidates the patient’s eligibility, the patient is withdrawn from the study.

Hospitalization for corticotomy and follow-up visits are carried out in accordance with the usual practices of each center.

If the investigator decides to perform a surgical revision before the 24-month visit after the initial surgery, the patient will not be withdrawn from the study but will be provided with follow-up until the normal end of the study, i.e., 24 months after the initial intervention.

In the event of an infectious recurrence or a complication requiring a new surgical intervention, the same follow-up schedule is set up after the surgery to replace the previous one and within the limit of the duration of the study (total follow-up of 24 months after the first intervention).

The end-of-study visit is the one scheduled 24 months (+/− 30 days) after the first corticotomy surgery. In the event of an infectious recurrence or complication requiring surgery and modifying the follow-up schedule, an end-of-study visit will be scheduled 24 months after the initial surgery specifically for the needs of the study.

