#### Statistical analysis

2.10.2.

The characteristics of the overall population and the two groups will be described. The analysis will be carried out on an intention-to-treat basis. Usual descriptive statistics will be presented for costs and QALYs. Depending on normality test results, mean costs will be compared across groups using Student’s t-test or non-parametric bootstrap. The 95% confidence interval for incremental cost-utility ratio will be computed using Fieller’s method or the bootstrap method. Deterministic sensitivity analyses will be performed, the results of which will be presented in a tornado diagram.

The statistical analysis to estimate the treatment effect on clinical outcomes will be based on the following methods: a linear regression model adjusted for stratification criteria for continuous variables; a logistic regression model adjusted for stratification criteria for dichotomous variables; and a Cox model adjusted for stratification criteria for survival data.

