This study has several limitations and particular biases. First, the complete adherence of the investigators is needed, especially if we focus on the training of the surgeons who manipulate the device, and only patients without post-debridement dead space management can be included. Secondly, it was impossible to blind the surgeon, who knows at the time of surgery, if the patient will receive or not the Cerament-G. It is of importance that the surgical debridement of the osteomyelitis of a particular patient has to be the same whether the patient is randomized to one arm or another. Finally, we decided, in particular to collect the data needed to estimate the informal care costs, to use a patient notebook to collect healthcare consumption. This mode of collection can lead to biases if the documents are not correctly completed. However, we closely monitor the filling of the patient notebooks and, if this is not satisfactory, we will consider linking the trial data with the National Health Data System (NHDS) in order to estimate the costs.

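### Three of the four early-withdrawal criteria can remove patients from the study after randomisation, which conflicts with the stated intention-to-treat analysis

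*Protocol article*

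**What the plan says.** Section 2.4.2 (Participant timeline) fixes the order of events: "If the committee confirms the patient’s eligibility, randomization is carried out and the patient assigned to one of the two study groups". Table 1 places randomisation at V1, between D-60 and D-2. Surgery is to be scheduled "no later than 2 months after the inclusion visit in order to limit the risk of canceling the surgery", and the same sentence treats cancellation as the patient leaving the study.

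Section 2.2.3 gives four criteria for early withdrawal from the study. The first, invalidation by the eligibility committee, comes before randomisation. The other three are:

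- Cancellation: the operation is called off for good.
- Flap: "Discovery (between the validation of the inclusion and the surgery) of the inability to perform the soft-tissue/muscle flap within 15 days", counted from the first operation.
- Laboratory findings: "Discovery of hypercalcemia or unknown severe renal failure between the inclusion visit and surgery".

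Section 2.10.2 states: "The analysis will be carried out on an intention-to-treat basis". On blinding, the Discussion says that "it was impossible to blind the surgeon, who knows at the time of surgery, if the patient will receive or not the Cerament-G".

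**The concern.** An intention-to-treat analysis compares everyone randomised, as randomised. A rule that takes randomised patients out of the study before surgery ends collection of their costs, utilities and recurrences, so the two statements cannot both be carried out in full. A later analysis plan can choose how to impute, but it cannot recover data that the protocol stopped collecting.

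The primary cost-utility result and the recurrence comparison would both be affected. If the removals differed between arms in number or in type of patient, the arms would no longer be comparable. Some of the criteria leave room for this. Cancellation and flap feasibility involve local judgement in a trial with an unblinded surgeon. The calcium and renal conditions appear in section 2.2.2 as contraindications to Cerament-G, so such a finding may carry different weight in the two arms.

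**Working it through.** **1. Timing of each criterion relative to randomisation**

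| Criterion (2.2.3) | Window | Position |
|---|---|---|
| Committee invalidation | Before validation | Before randomisation |
| Surgery definitively cancelled | No limit stated | Can be after |
| Flap not feasible within 15 days | Validation to surgery | Essentially after |
| Hypercalcaemia or severe renal failure | Inclusion visit to surgery | Spans randomisation |

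Table 1 schedules the calcium and creatinine tests at V1 and again at D0, so the last check falls after allocation.

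**2. What withdrawal means here**

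Section 2.4.2 says that a patient who needs surgical revision is not withdrawn and is followed to 24 months. Withdrawal from the study is therefore used for something more than a change of treatment. The final visit (2.4.2) and the economic horizon (2.7.1) both run from the initial surgery, so a randomised patient who is never operated on has no defined 24-month outcome.

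**3. The plan's own sample size**

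Inputs from section 2.10.1: 20% versus 6%, two-sided alpha 0.05, power 80%, about 10% early withdrawal. With pooled variance and no continuity correction, and a mean rate of 0.13:

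n = [1.960 × √(2 × 0.13 × 0.87) + 0.842 × √(0.20 × 0.80 + 0.06 × 0.94)]² / 0.14² ≈ 89.4, so 90 per group.

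90 / 0.9 = 100 per group, 200 in total. This reproduces the stated figure. Other forms, after the same inflation, give 116 (continuity-corrected), 97 (unpooled) or 94 (arcsine) per group.

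The plan thus allows for about 10 randomised patients per group who do not contribute. Committee invalidations are counted separately (220 included, 200 randomised). The article does not break the 10% down by reason.

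**4. Power if everyone is kept**

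- 90 analysed per group, 20% versus 6%: 80.3%.
- 100 per group, same rates: 84.3%.
- 100 per group, assuming 5% of the device arm never receives the device and has the 20% risk: 0.95 × 6% + 0.05 × 20% = 6.7%, power 79.4%.
- Same with 10%: 0.90 × 6% + 0.10 × 20% = 7.4%, power 74.0%; 116 analysed per group would be needed for 80%.

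**5. Possible bias from one-sided removal (assumed inputs)**

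Let p be the true rate in an arm, w the share withdrawn, and k their risk relative to the arm average. The observed rate is (p − w·k·p) / (1 − w). With p = 20%:

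- w = 5%, k = 1.5: (0.20 − 0.015) / 0.95 = 19.5%, a shift of 0.5 points.
- w = 10%, k = 2: (0.20 − 0.04) / 0.90 = 17.8%, a shift of 2.2 points.
- w = 10%, k = 3: (0.20 − 0.06) / 0.90 = 15.6%, a shift of 4.4 points.

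If both arms have the same p, w and k, the spurious difference is zero.

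**The case against.** The strongest reply has four parts.

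- **Knowledge of the arm.** A reader might infer that the withdrawal decisions are taken by teams who know the allocation. The documents do not say so. The Discussion speaks only of the time of surgery, and the article states neither when the centre learns the allocation nor who applies the criteria. What stands is that no concealment until surgery is described.
- **Exclusion from the analysis.** The article does not say that withdrawn patients leave the analysis set, and that definition may sit in a full protocol or analysis plan that is not shown. The 10% inflation shows an allowance for missing information and is not a rule of exclusion. This is correct, but the conflict remains: a patient withdrawn from the study supplies no outcomes, so keeping that patient in the analysis would rest on imputation.
- **Neutral criteria.** The criteria apply to both arms, the laboratory findings are objective, and they are exclusion criteria for the whole trial. The committee has also considered closure or flap before randomisation. This stands, and it makes differential withdrawal a risk only. It does not remove the discretion in cancelling surgery or in judging a flap infeasible later.
- **Debridement.** A reader might go further and argue that allocation must be withheld until debridement is finished. The article already discloses the unblinded surgeon as a limitation, says that debridement must not differ between arms, and has recurrence confirmed by a blinded independent committee. Recruitment began in October 2021, so a move to allocation in theatre would create two allocation regimes in one trial. That is a design preference and does not correct an error.

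**Conclusion.** The conflict is real and rests on the text alone: three of the four criteria in section 2.2.3 can take randomised patients out of the study, while section 2.10.2 promises an intention-to-treat analysis. The missing time origin for unoperated patients adds to it.

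The bias is possible but not demonstrated, and the documents do not give its size. The range of 0.5 to 4.4 points, at most about a third of the 14-point target (4.4 / 14 = 0.31), depends wholly on the assumptions of removal from one arm only, 5 to 10% removed, and 1.5 to 3 times the average risk. It should not be read as an estimate. The sample size is correct on its own inputs.

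Power is not the main argument. Keeping everyone gains up to 4 percentage points (84.3% against 80.3%) without dilution, and dilution of 5% uses up that gain. The reason to act is that the randomised comparison is protected only if outcomes continue to be collected.

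**What to change.** Amend sections 2.2.3 and 2.4.2 as follows.

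1. Restrict withdrawal from the study to events before randomisation.
2. State that, after randomisation, a patient may leave the assigned procedure on clinical grounds but stays in follow-up and in the intention-to-treat set. Clinical decisions are not touched.
3. Define a time origin for patients who are never operated on, for example 24 months from randomisation or from the planned surgery date.
4. Report departures after randomisation by arm and by reason.

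The cost is amendment wording, follow-up of a few unoperated patients, and some dilution: on the assumptions above, power is 79.4% if 5% of the device arm never receives the device, and 74.0% if 10% does not.

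Optionally, where centres find it feasible, the existing web system could release the allocation closer to surgery, after the last eligibility check, which would shorten the window in which these events can occur. Allocation in theatre after debridement is not part of the required change.

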### Randomization

2.3.

Patients will be randomized between the two strategies in a balanced manner with a computerized and secure system *via* the internet. Randomization will be carried out by minimization, using a computer algorithm that calculates in real time the allocation of the group that guarantees the best possible balance, taking into account the patient’s stratification values (center and preventive stabilization) as well as the patients already randomized. So that the randomization is not predictable, a part of randomness will be added to the algorithm.

### Experimental design

2.4.

#### Study treatments

2.4.1.

Cerament-G is an absorbable ceramic bone substitute composed of calcium sulfate, hydroxyapatite, and gentamicin sulfate, intended to fill bone gaps and deficits in the skeleton and promote bone healing. This is a medical device with CE marking since February 11, 2013, and manufactured by the Bonesupport laboratory (Lund, Sweden). The product, supplied in 5 ml or 10 ml format, consists of a powder and a liquid component. The powder contains 40% hydroxyapatite and 60% calcium sulfate hemihydrate. The liquid component is saline solution and gentamicin. The mixture of the components gives a viscous material suitable for direct or percutaneous injection into a bone void. By combining hydroxyapatite and calcium sulfate, an optimal balance is achieved between the rate of implant resorption and the rate of growth in bone. Calcium sulfate acts as an absorbable carrier for hydroxyapatite. Hydroxyapatite, a substance with a low resorption rate and a high osteoconductive profile that promotes bone growth, provides long-term structural support for new bone tissue. The hardened material facilitates bone growth and based on the observation of serial x-rays in a large number of patients and various conditions, it appears to be replaced by bone over a period of 6 to 12 months.

Cerament-G mixed contains 17.5 mg of gentamicin per ml of paste. Gentamicin prevents colonization of microorganisms sensitive to gentamicin in order to protect bone healing. Gentamicin is bactericidal against a wide range of bacterial infections, mainly Gram-positive bacteria like Staphylococcus, but also many Gram negative bacteria including Pseudomonas, Proteus, Serratia, which are also found in chronic osteomyelitis.

Cerament-G is indicated for use as a bone void filler material in a surgical procedure where there is a risk of bacterial contamination. It is therefore indicated to fill gaps and bone deficits in the skeleton that do not involve the stability of the bone structure, especially in the limbs. These bone defects may appear spontaneously or have been created surgically or following trauma to the bone, have been identified during primary surgery or surgical revision. It can also be bone defects identified around rigid implant devices.

Cerament-G will be used in this study for the management of patients with chronic osteomyelitis in the innovative strategy, as an adjunct during surgery usually performed by corticotomy. It will be used in accordance with the indications of the CE marking and its instructions for use. The volume of Cerament-G used during the intervention will be planned according to the volume of the cavity to be filled; it is on average 15 ml and cannot exceed the maximum volume corresponding to a gentamicin concentration of 6 mg/kg of patient weight. The volume to be administered will be discussed at a meeting of the eligibility validation committee, which will propose an optimal volume given the characteristics of the patient. In the event of a very large defect, the use of part of the volume of Cerament-G to form beads (or pellets) may be proposed, which would contribute to the best possible filling while limiting the total volume to be used.

#### Participant timeline

2.4.2.

The first inclusion took place on October 14, 2021. Total inclusion period is expected to be 3 years and the duration of participation of each patient will be 25 months. Schedule for enrolment, interventions and assessments are summarized in Table 1.

**Table 1 tab1:** Schedule for enrolment, interventions and assessments.

Moment actions	STEPS							
	V1 Inclusion	V2 Hospitalization / Corticotomy	V3 Follow-up consultation	V4 Follow-up consultation	V5 Follow-up consultation	V6 Follow-up consultation	V7 Follow-up consultation	V8 End of study
	D-60 à D-2	D0	W + 4/W + 6	M3 +/− 15 d	M6 +/− 15 d	M12 +/− 15 d	M18 +/− 30 d	M24 +/− 30 d
Informed consent	X							
Randomization	X							
Antecedents	X							
Urine pregnancy test (only for women of childbearing age)	X							
Physical examination	X		X	X	X	X	X	X
Determination of calcium, phosphorus, albumin, urea, and creatinine (serum creatinine and creatinine clearance / measurement of GFR)	X	X	X	X				
EQ-5D-5L^a^	X		X	X	X	X	X	X
Resource consumption			X	X	X	X	X	X
Professional and informal help	X		X	X	X	X	X	X
Micro-costing^b^		X						
Corticotomy / fracture complication		X	X	X	X	X	X	X
Acute renal failure		X	X	X				
Healing and bone remodeling / consolidation (standard radiology)	X					X		
Infectious recurrence		X	X	X	X	X	X	X
Surgical revision^c^			X	X	X	X	X	X
Amputation			X	X	X	X	X	X
Adverse events	X	X	X	X	X	X	X	X

a In the event of surgical revision, an EQ-5D will be completed by the patient closest to the event.

b Micro-costing will only be carried out for patients included in the innovative strategy, with the use of Cerament-G.

c In the event of surgical revision, the schedule begins again in accordance with post-surgical follow-up, until the normal end of the study, i.e., 24 months after the first corticotomy, is reached.

Patients with chronic osteomyelitis of the long bones (stage III of the Cierny-Mader classification) will be identified during the multidisciplinary meeting carried out within the participating CRIOAc.

The patient, if eligible, is informed of the completion of the study during a visit carried out with a view to planning his surgical intervention (pre-surgical visit) or during a dedicated visit, by the investigator. A written information leaflet is given to the patient.

The pre-surgical visit and the necessary examinations are carried out in accordance with usual practices. Hospitalization for the corticotomy is scheduled in accordance with the usual management no later than 2 months after the inclusion visit in order to limit the risk of canceling the surgery and therefore of the patient leaving the study prematurely.

The eligibility validation committee will meet to validate the patient’s inclusion in the study, based on available clinical data and imaging. If the committee confirms the patient’s eligibility, randomization is carried out and the patient assigned to one of the two study groups: the standard of care (usual medico-surgical management) or the innovative strategy (medico-surgical management with the use of Cerament-G during corticotomy surgery). If the committee invalidates the patient’s eligibility, the patient is withdrawn from the study.

Hospitalization for corticotomy and follow-up visits are carried out in accordance with the usual practices of each center.

If the investigator decides to perform a surgical revision before the 24-month visit after the initial surgery, the patient will not be withdrawn from the study but will be provided with follow-up until the normal end of the study, i.e., 24 months after the initial intervention.

In the event of an infectious recurrence or a complication requiring a new surgical intervention, the same follow-up schedule is set up after the surgery to replace the previous one and within the limit of the duration of the study (total follow-up of 24 months after the first intervention).

The end-of-study visit is the one scheduled 24 months (+/− 30 days) after the first corticotomy surgery. In the event of an infectious recurrence or complication requiring surgery and modifying the follow-up schedule, an end-of-study visit will be scheduled 24 months after the initial surgery specifically for the needs of the study.

